### Sample size and power

The primary outcome is the change in TFI from baseline to follow-up at three months. A TFI decrease of 13 points is considered a minimal clinically important difference. Assuming a standard deviation (SD) of 20 points (SD found in international literature [44] as well as in a previous study of our research group [45]) and a significance level of 0.05, an achieved sample size of 39 per group is required to detect an effect of 13 points with 80% power using a two-sample t-test. Taking into account a possible 20% drop-out, 50 patients will be recruited into each group. Hence, a total of 100 patients will be recruited for the study.

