#### Statistical methods

Data will be analyzed using SPSS statistical software version 25 (SPSS Inc., Chicago, IL, USA). The primary outcome is the change in TFI from baseline to three months after the treatment. A linear regression model using delta TFI (pre minus post therapy) as an outcome and treatment as a predictor with correction for age, gender, hearing loss, HADS score, and TFI grade will be used as primary outcome analysis. All patients will be used in an intention-to-treat (ITT) analysis.

Per-protocol analyses will be performed for all secondary outcome measurements to evaluate the treatment effect for the compliers. The change in secondary outcomes (which are all continuous variables) from baseline to follow-up at three months will be analyzed with a linear regression model with treatment as predictor controlling for age, gender, hearing loss, HADS score, and TFI grade. The questionnaires that are administered repeatedly over time will be modelled by a linear mixed model using patient as a random intercept to correct for repeated measures coming from the same patient. The Holm-Bonferroni method will be used to correct for multiple testing.

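### Change scores are not adjusted for the outcome's own continuous baseline, which costs precision mainly in secondary outcomes measured only at baseline and three months

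*Protocol article*

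**What the plan says.** All references are to the protocol article.

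- **Primary model (Statistical methods).** Delta TFI, pre minus post, is regressed on treatment "with correction for age, gender, hearing loss, HADS score, and TFI grade will be used as primary outcome analysis".
- **Secondary models (same section).** The changes to three months, all described as continuous, "will be analyzed with a linear regression model with treatment as predictor controlling for age, gender, hearing loss, HADS score, and TFI grade". The list is the same one, whichever outcome is analysed.
- **Repeated questionnaires (same section).** These are also modelled with a linear mixed model with a random intercept per patient. How baseline enters that model is not stated.
- **Measurement times (Interventions).** The full test battery is done at T0 and at three months. Questionnaires are also completed right after the last session and at six months. Pitch and loudness match, SPIQ/SPIN, RBANS-H and CAEP therefore have two time points only.
- **Allocation.** Randomisation is stratified by gender and four TFI grades.
- **Sample size and power.** The calculation concerns the TFI alone: "an achieved sample size of 39 per group is required to detect an effect of 13 points with 80% power using a two-sample t-test".

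**The concern.** In a model for change, the outcome's own baseline is usually the strongest predictor, because high starting values tend to fall and low ones to rise. If it is left out, that variation stays in the error term. A chance difference between the groups at baseline also passes into that trial's estimate through regression to the mean.

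This is a stated choice of covariates, not a detail left to an analysis plan: an analysis plan that followed the text would carry the loss over. For most secondary outcomes nothing in the list is the outcome's own baseline. For the primary, the 0–100 score enters only as a four-level grade. At stake are wider confidence intervals than the collected data need give, mainly for secondary outcomes.

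**Working it through.** **1. The plan's own figure.** Inputs from Sample size and power: difference 13, SD 20, significance level 0.05 (two-sided reproduces the stated figure), power 80%. The normal approximation gives n = 2 × [20 × (1.960 + 0.842)/13]² = 37.2, so 38 per group. The exact t calculation gives 39 (power 0.809 at 39, 0.799 at 38). Dropout: 39/0.8 = 48.75, so 49, rounded up to 50 in the plan. The stated figure holds. It rests on an unadjusted t-test and does not depend on this point.

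**2. Formula.** Take equal variance (set to 1) before and after treatment, and let r be the correlation between baseline and three months. Let g be the correlation between the outcome's own baseline and the covariates already in the model, assumed to predict follow-up only through that baseline.

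- Residual variance, planned change model: (1 − r)²(1 − g²) + (1 − r²)
- Residual variance, with own baseline added: 1 − r²
- At g = 0 the ratio of the second to the first is (1 − r²)/[2(1 − r)] = (1 + r)/2

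Example, r = 0.5 and g = 0: planned 0.25 + 0.75 = 1.00, with own baseline 0.75. The planned model has 33.3% more variance; equivalently, adjustment saves 25%.

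**3. Range.** The article gives neither r nor g, so both are assumptions. Each cell shows excess variance of the planned model / saving from adding own baseline.

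| g | r = 0.5 | r = 0.7 | r = 0.8 | r = 0.9 |
|---|---|---|---|---|
| 0 | 33.3% / 25% | 17.6% / 15% | 11.1% / 10% | 5.3% / 5% |
| 0.3 | 30.3% / 23% | 16.1% / 14% | 10.1% / 9% | 4.8% / 5% |
| 0.5 | 25.0% / 20% | 13.2% / 12% | 8.3% / 8% | 3.9% / 4% |
| 0.7 | 17.0% / 15% | 9.0% / 8% | 5.7% / 5% | 2.7% / 3% |

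The row g = 0 is the ceiling. As an illustration only: with 39 per group and an effect that own-baseline adjustment would detect with 80% power, the planned model at g = 0 has about 68%, 73% and 76% power at r = 0.5, 0.7 and 0.8. That corresponds to about 29, 33 and 35 effective patients per group (39/1.333, 39/1.176, 39/1.111).

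**4. Primary TFI.** Assume a baseline distributed as normal (50, 20), truncated to the entry range 24–90, and cut into four grades. Mean 50 and the range are from the article; the baseline SD, shape and cut-offs are assumed. Grade then explains about 88–91% of baseline variance. Putting 0.885 and 0.91 in place of g²:

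- r = 0.5, 0.885: 0.25 × 0.115/0.75 = 3.8% excess, a saving of 3.7%
- r = 0.8, 0.91: 0.04 × 0.09/0.36 = 1.0% excess, a saving of 1.0%

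A second parametrisation fixes the SD of change at 20 and varies the baseline-to-follow-up slope from 0.4 to 0.7. It gives about 0.5–3%; at slope 0.5, for example, residual variance is 344.9 with grade and 339.4 with the continuous score, a saving of 1.6%. Together the range is about 0.5–4%.

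**5. Which outcomes are affected.**

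- *Pitch and loudness match, SPIQ/SPIN, RBANS-H, CAEP:* two time points, change regression only, own baseline absent. The loss is clearest here.
- *TQ, SSQ12, VAS, HQ, HUI23:* the same loss in the change regression. In the mixed model, free baseline means with a random intercept make the three-month contrast a difference in change scores again. Precision is recovered only if baseline is a covariate or baseline means are constrained equal between groups.
- *HADS:* its own baseline is in the list, reading HADS score as the baseline value. *Audiometry:* largely covered through hearing loss, depending on how that is defined.

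**The case against.** The strongest reply is that nothing here is invalid. Under randomisation the planned estimates are unbiased, the sample size reproduces, and the primary analysis already adjusts for, and balances allocation on, a coarse form of its own baseline. All of that stands. A reader might infer that the primary analysis is biased, materially weakened or underpowered. The article does not support that: the primary gain is a few percent at most.

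A reader might also infer that every secondary outcome loses up to a quarter of its precision. That does not follow either. HADS and audiometry are wholly or largely covered. Hearing loss may stand in for part of baseline SPIQ/SPIN, SSQ12 and loudness match, and TFI grade for part of baseline TQ. The repeated questionnaires have a mixed model that could recover the loss, and leaving its handling of baseline to an analysis plan is no fault in an article.

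Finally, the article claims no power for secondary outcomes, calls RBANS-H and CAEP explorative, and does not say which tests the Holm-Bonferroni correction covers. An argument that multiplicity makes this loss critical would therefore be inference. What remains is a stated regression that gives up precision without any benefit in return.

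**Conclusion.** The point holds as a matter of efficiency, not validity. One covariate list is fixed for all change scores, and it omits the analysed outcome's continuous baseline. The consequence is clearest for pitch and loudness match, SPIQ/SPIN, RBANS-H and CAEP, with a ceiling of 25% of residual variance at r = 0.5, falling to 5% at r = 0.9. The actual figure is lower by an unknown amount wherever TFI grade, HADS or hearing loss carries part of the baseline. For the repeated questionnaires it applies to the change regression, and to the mixed model only if baseline means are left free. For the primary TFI it is about 0.5–4%.

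These sizes rest on equal variances before and after treatment and on assumed correlations and grade cut-offs; the article gives none of them. The direction is the same across the ranges examined.

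**What to change.** In each change regression, add the continuous baseline value of the outcome being analysed and keep the existing covariates. For the primary, add continuous baseline TFI and keep gender and TFI grade as allocation factors. In the mixed models, either enter the continuous baseline as a covariate with only post-baseline values as responses, or keep baseline as a response and constrain its mean to be equal in the two groups. HADS needs no change beyond confirming that the covariate is the baseline score; for audiometry, define hearing loss so that it is clear whether the analysed threshold's own baseline is included.

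The cost is a sentence of text and one degree of freedom per model. All these baselines are already collected at T0, so no new data, visits or patients are needed. The change should be fixed before unblinding, so that the choice of covariates cannot appear to follow the results.

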**Fig. 2 Fig2:**
[figure not shown]
Schedule of enrolment, interventions, and assessments in accordance with the SPIRIT 2013 guidelines. tDCS transcranial direct current stimulation, TFI Tinnitus Functional Index, RBANS-H Repeatable Battery for the Assessment of Neuropsychological status adjusted for hearing-impaired individuals, CAEP cortical auditory evoked potentials

When patients are enrolled in the study, six sessions of sequential dual-site HD-tDCS (or sham stimulation for the control group) are planned within three weeks’ time (twice per week, with at least one day between sessions: T_a_ - T_f_). Stimulation (or sham) is provided for 30 min each session. The electrodes are positioned at the rDLPFC and the LTA. The positioning is according to the 10/20 international system for EEG electrode placement. For the rDLPFC stimulation, the central anode will be placed at F4 and the adjoining cathodes at F2, F6, FC4, and AF4 [24]. For the LTA stimulation, the central anode is positioned at CP5 with adjoining cathodes at C5, TP7, CP3, and P5. A constant current of 2 mA is applied for 15 min at each site with a fade-in and fade-out of 20s, resulting in a total stimulation duration of 30 min. For the sham stimulation, constant current will only be applied for 20s as previously described [30]. The direct current is transmitted by means of five sintered silver/silver chloride (Ag/AgCl) ring electrodes with inner radius of 6 mm and outer radius of 12 mm and delivered by a battery-driven Soterix Medical 1 × 1 tDCS low-intensity stimulator and 4 × 1 multichannel stimulation adaptor (Soterix Medical Inc., New York, NY, USA) with a maximum output of 2 mA. The ring electrodes are stabilized using HD-Electrode holders hooked in the Soterix Medical HD-cap and filled with EEG electrode gel (Neurax, Bonheiden, Belgium) following the guidelines for 4 × 1 HD tDCS stimulation [22].

Immediately after the last HD-tDCS session (T_f_), the patient is instructed to fill in all questionnaires. A follow-up (T_1_) at three months after the baseline measurements will contain the full clinical study protocol: pure tone audiometry, tinnitus analysis, SPIQ/SPIN, questionnaires, RBANS-H, and CAEP. A second follow-up (T_2_) is planned at six months after baseline measurements, comprising only the complete set of questionnaires.

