Except for mild itching or tingling sensations, headaches, or fatigue, no adverse effects of HD-tDCS treatment are expected. In case patients do report serious side effects, HD-tDCS treatment will be discontinued.

No concomitant tinnitus treatment will be allowed between baseline measurement and the three-month follow up. After the three-month time point, participants will be allowed to undergo additional treatment. If participants were allocated to the sham group, they will have the right to undergo an actual HD-tDCS treatment free of cost after the three-month time point.

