### Assignment of interventions

#### Allocation

Participants will be randomized into the treatment group or the placebo group in a 1:1 ratio. The randomized list will be generated by an independent researcher using QMinim Online Minimization®. The allocation sequence will depend on the date on which participants are referred to the trial. Stratified randomization according to the grade of tinnitus severity on the TFI and gender will be performed. The TFI categorizes patients from grade 1 (slight tinnitus distress) to grade 5 (severe tinnitus distress). As patients with grade 1 are generally not in need of intervention, they will be excluded from the study (inclusion criterion: TFI > 24). Therefore, a total of eight strata will be defined by TFI grade and gender. Patient enrollment and allocation will be performed by an independent researcher.

In order to avoid any test bias, the researcher performing the baseline and follow-up measurements is blinded to the allocation of the patient. The investigator will be unblinded by an independent researcher after the three-month time point (T_1_). The independent researcher will be able to access the randomization sequence via QMinim, an online portal. For technical reasons, it is not possible to blind the investigator administering the HD-tDCS. Therefore, for each patient, the investigator administering the HD-tDCS will differ from the researcher performing the baseline and follow-up measurements.

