#### Blinding

Both the patient and the investigator performing baseline and three-month follow-up measurements will be blinded up until and including the three-month time point (T_1_). Patients will be unblinded by an independent clinician at a separate hospital visit following the three-month follow-up time point.

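### The mixed model for the repeated questionnaires has no three-month limit, so on its plain reading it takes in six-month scores collected after unblinding and possible crossover

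*Protocol article*

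**What the plan says.** Under Interventions, questionnaires form part of the baseline visit (T0). Right after the last session (Tf) "the patient is instructed to fill in all questionnaires". They are repeated at T1, three months after baseline. A further visit, T2, "is planned at six months after baseline measurements, comprising only the complete set of questionnaires".

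The same section changes the treatment conditions once T1 has passed: "After the three-month time point, participants will be allowed to undergo additional treatment". Of patients allocated to sham it says that "they will have the right to undergo an actual HD-tDCS treatment free of cost after the three-month time point". The blind ends at the same point. Under Blinding: "Patients will be unblinded by an independent clinician at a separate hospital visit following the three-month follow-up time point". Under Allocation: "The investigator will be unblinded by an independent researcher after the three-month time point".

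Statistical methods fixes the primary analysis at three months. It also fixes the secondary change scores there, since the change "from baseline to follow-up at three months will be analyzed with a linear regression model with treatment as predictor". The next sentence reads: "The questionnaires that are administered repeatedly over time will be modelled by a linear mixed model using patient as a random intercept". It names no visits and no time or treatment-by-time terms, and it gives no rule for scores obtained after T1. Holm-Bonferroni correction follows.

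**The concern.** T2 consists only of questionnaires, and the mixed model is the only analysis in the article that could use them. The neighbouring regressions carry a three-month limit and this one does not, so the natural reading is that T2 enters.

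By T2 the sham arm may be a mixture of patients with no further treatment, patients who have had active HD-tDCS and patients who have had something else. The active arm may also have had other treatment. Every score is then a self-report by someone who knows the allocation. An arm difference at T2, or one averaged over visits that include T2, does not estimate HD-tDCS against sham, which is the comparison in the trial's hypothesis.

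If HD-tDCS works, crossover pulls the difference towards zero. Unblinded self-report and other treatments could move it either way. A benefit that truly persists could then look like one that wears off between three and six months.

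**Working it through.** **Inputs from the protocol (Sample size and power):** effect 13 TFI points, SD 20, significance level 0.05, 80% power, 39 per group, 20% drop-out, 50 per group recruited.

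**Reproducing the plan's own figure.** The exact two-sided two-sample t-test has 79.9% power at 38 per group and 80.9% at 39, so 39 is correct. Allowing for drop-out, 39/0.80 = 48.75, or 49, against the 50 planned. The sample size is sound, and it concerns the three-month TFI change only.

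**Assumptions not in the protocol:** the 13-point benefit is present at Tf, T1 and T2; a share p of sham patients has had active treatment by T2; each of them has the full benefit by then; unblinding and other treatments add nothing.

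**Formulas**

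- Contrast at T2: 13 × (1 − p)
- One common effect over Tf, T1 and T2, equally weighted: [13 + 13 + 13(1 − p)]/3 = 13 × (1 − p/3)

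| p | T2 contrast | Common effect |
|---|---|---|
| 0% | 13.0 | 13.0 |
| 25% | 9.75 | 11.9 |
| 50% | 6.5 | 10.8 |
| 75% | 3.25 | 9.75 |
| 100% | 0 | 8.7 |

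**Check by simulation.** Random-intercept models were fitted to Tf, T1 and T2 with baseline as a covariate, 50 per arm, total SD 20 and 150 replicates. The within-patient correlation of 0.5 is a further assumption. Each cell gives the mean estimated benefit with complete data / with 20% of post-baseline scores missing at random.

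| p | One common effect, T2 included | T1 contrast, treatment-by-visit | T2 contrast, treatment-by-visit | One effect, Tf and T1 only |
|---|---|---|---|---|
| 0% | 13.4 / 13.1 | 13.2 / 13.2 | 13.6 / 13.0 | 13.3 / 13.2 |
| 50% | 10.8 / 10.5 | 12.8 / 12.7 | 6.5 / 6.0 | 12.9 / 12.8 |
| 100% | 8.8 / 8.5 | 12.9 / 12.5 | 0.2 / −0.3 | 13.1 / 12.9 |

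The estimates vary between replicates with an SD of 2.4 to 4.0, so each mean carries a simulation error of about 0.2 to 0.3 points (2.4/√150 to 4.0/√150). The results agree with the formulas. With a common effect, the contamination reaches the reported result. With treatment-by-visit terms, it stays in the T2 contrast. With the model cut at T1, the true 13 points are recovered whatever the crossover share.

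**The case against.** The best counter-argument is that the protocol never says T2 enters the model. T0, Tf and T1 are already repeated measurements, and the preceding sentence is limited to three months. Fixed effects and the visits used are also details that an article often leaves to an analysis plan. This is fair as to certainty: inclusion of T2 is the plainer reading, not an explicit statement. It does not remove the point. The protocol itself creates the unblinding and crossover, and then names a model whose wording takes in the affected data while limiting its neighbours.

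The secondary paragraph also opens with per-protocol analyses aimed at compliers, which might be thought to remove patients who crossed over. But active treatment of sham patients after T1 is permitted, so it is not a deviation and would not obviously exclude anyone.

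The objection to the size is sound. The crossover shares have no source in the document. Full benefit by T2 is generous, because an unblinding visit and a course of treatment must first fit between months three and six. The 13-point and SD 20 inputs belong to the TFI at three months and do not carry over to the other questionnaires. No six-month comparison was powered, so a loss of power at T2 would not be a loss of anything the trial claims.

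A reader might infer that the trial's main randomised comparison is biased. The documents do not support that. The primary outcome and the secondary change scores are taken at T1, and blinding is stated to hold up to and including T1.

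**Conclusion.** The point holds as a moderate defect in a secondary analysis. On its plain reading the mixed model includes six-month scores that cannot support a comparison of HD-tDCS with sham, and nothing in the article separates them from the blinded scores.

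The consequence depends on a choice the article does not state. With one treatment effect over visits, that effect shrinks by the factor 1 − p/3: to 83% of its value at 50% crossover (10.8 of 13 points) and to 67% at full crossover (8.7 of 13). This assumes a lasting effect, full benefit after crossover and equal weight for the three visits. With treatment-by-visit terms, the T1 contrast is essentially intact and only the T2 contrast fails. Bias from unblinded self-report and other treatments would come on top, in a direction that cannot be predicted.

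It would go too far to say that the plan definitely pools T2 into one effect, or to treat the figures as a forecast. They show the mechanism under stated assumptions.

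**What to change.** State in Statistical methods that between-arm inference from the mixed model uses T0, Tf and T1 only, with treatment-by-visit terms. Report T2 separately, labelled as unblinded and post-crossover, descriptively by original arm and by treatment received after T1. Keep it outside the Holm-Bonferroni family. This requires a record of any tinnitus treatment started between T1 and T2.

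The cost is a change of analysis wording and, if it is not already collected, one data item at T2. The sample size, visits and primary analysis stay as they are. What is given up is a six-month contrast of active against sham, which the design cannot support.

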**Methods:**

This study proposes a randomized, double-blind, placebo-controlled trial with parallel group design. A total of 100 chronic tinnitus patients will be randomly allocated to an experimental group or a sham group, with allocation stratified according to gender and tinnitus severity. Patient and researcher will be blinded to the patient’s allocation. Patients will undergo six sessions of sequential dual-site HD-tDCS of the left temporal area and the right dorsolateral prefrontal cortex. Evaluations will take place at baseline, immediately following treatment, and at three and six months after the start of the therapy. The primary outcome measure is the change in Tinnitus Functional Index (TFI) score. Secondary outcome measures include audiological measurements, cortical auditory evoked potentials, the Repeatable Battery for the Assessment of Neuropsychological Status adjusted for hearing-impaired individuals (RBANS-H), and supplementary questionnaires probing tinnitus severity and additional symptoms. By use of a linear regression model, the effects of HD-tDCS compared to sham stimulation will be assessed.

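### The random-intercept mixed model for the secondary questionnaires forces equal correlation on unevenly spaced visits, so visit-specific standard errors can be wrong in either direction

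*Protocol article*

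**What the plan says.** The abstract sets the visits: "Evaluations will take place at baseline, immediately following treatment, and at three and six months after the start of the therapy". The Interventions section adds the detail. Sessions are planned within three weeks, and at the end "Immediately after the last HD-tDCS session (T_f_), the patient is instructed to fill in all questionnaires". T1 is three months after baseline with the full test protocol. T2 is six months after baseline with questionnaires only. Other tinnitus treatment, including active stimulation for sham patients, is allowed after the three-month visit, and the Blinding section has patients unblinded after that visit.

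Statistical methods gives three models:

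- Primary: "A linear regression model using delta TFI (pre minus post therapy) as an outcome and treatment as a predictor", with covariates.
- Secondary outcomes: "The change in secondary outcomes (which are all continuous variables) from baseline to follow-up at three months will be analyzed with a linear regression model", adjusted for the same covariates.
- Repeated questionnaires: a "linear mixed model using patient as a random intercept to correct for repeated measures coming from the same patient". No other device for the within-patient dependence is named.

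One further sentence covers multiplicity: "The Holm-Bonferroni method will be used to correct for multiple testing". The article does not state the fixed effects of the mixed model or which contrast will be reported from it.

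**The concern.** A patient random intercept with independent residuals implies that any two visits of the same patient are equally correlated and, by default, that the variance is constant. The design gives two reasons to doubt this. The gaps between visits run from about three weeks to six months, and treatment is no longer controlled between T1 and T2. When the true correlations differ by pair, the model averages them. A contrast between two visits that are more alike than average then gets too large a standard error, and a contrast between less similar visits gets too small a one. Tf and T2 matter most, because the plan names no other analysis for them. At stake are the immediate effect, which could be missed, and the six-month comparison, which could look firmer than it is.

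**Working it through.** **The plan's own figure.** For a 13-point difference, SD 20, two-sided 0.05 and a two-sample t-test, noncentral-t power is 79.9% with 38 per group and 80.9% with 39. The stated 39 is therefore right. 39/0.8 = 48.75, so 49, and the plan recruits 50. None of this uses the mixed model.

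**Inputs.** Visit times are 0, 0.7, 3 and 6 months (0.7 for about three weeks). The article gives no between-visit correlations, so every correlation below is an assumption. I also assume complete balanced data and arm-by-visit fixed effects.

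**Formulas.** For the change from T0 to visit j:

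- model variance = 2 × (mean variance − mean covariance), averaged over all visits;
- true variance = Var(T0) + Var(j) − 2 Cov(T0, j);
- SE ratio R = √(model variance / true variance);
- actual type I error at nominal 5% = 2 × [1 − Φ(1.96 R)].

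With equal variances the SD cancels: R² = (1 − mean correlation) / (1 − correlation of T0 with j).

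**Calendar-time decay, correlation = ρ^(gap/3).**

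For ρ = 0.5 the six correlations are 0.8507 (T0-Tf), 0.5 (T0-T1), 0.25 (T0-T2), 0.5878 (Tf-T1), 0.2939 (Tf-T2) and 0.5 (T1-T2). Their mean is 0.4971.

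- T1: √(0.5029/0.5) = 1.003, error 4.9%.
- Tf: √(0.5029/0.1493) = 1.84, error below 0.1%.
- T2: √(0.5029/0.75) = 0.82, error 11%.

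For ρ = 0.8 the mean correlation is 0.7844.

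- T1: √(0.2156/0.2) = 1.038, error 4.2%.
- Tf: √(0.2156/0.0507) = 2.06, error below 0.1%.
- T2: √(0.2156/0.36) = 0.77, error 13%.

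T1 comes out nearly right because its three-month gap is close to the mean gap: (0.7 + 3 + 6 + 2.3 + 5.3 + 3)/6 = 3.4 months. That depends on T2 being in the model. With T0, Tf and T1 only, the ratio at T1 is 0.841 (ρ = 0.5) to 0.825 (ρ = 0.8), and the error is about 10%.

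**Other assumed structures, T1 contrast, four visits.**

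| Structure | SE ratio | Type I error |
|---|---|---|
| Compound symmetry | 1.00 | 5.0% |
| AR(1) by visit order, 0.6 to 0.9 | 0.92 to 0.91 | 7.1 to 7.3% |
| Pre-post 0.7, post-post 0.8 | 0.91 | 7.4% |
| Pre-post 0.5, post-post 0.8 | 0.84 | 10.1% |
| T2 decorrelated (0.40, 0.45, 0.50 with T0, Tf, T1) | 1.10 | 3.1% |
| Same, T2 SD 20% larger | 1.18 | 2.0% |

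For the pre-post 0.5 row the mean correlation is (3 × 0.5 + 3 × 0.8)/6 = 0.65, so R = √(0.35/0.5) = 0.837. The same figure applies at Tf and T2.

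**Checks.** REML fits to 300 simulated null trials with 40 per arm rejected at T1 in 6.3% (compound symmetry), 4.0% (decay, ρ = 0.7) and 10.3% (pre-post 0.5, post-post 0.8). The Monte Carlo standard error near 5% is √(0.05 × 0.95/300) = 1.3 points, so these agree with the closed form. If baseline were instead a covariate and only post-baseline visits were modelled, the T1 ratio would run from 0.93 to 1.15 (error 6.7% to 2.4%), and it would be 1.00 in the pre-post/post-post rows.

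**The case against.** A reader might infer that the three-month standard error is wrong and the test anticonservative. The documents do not support that. They give no correlations and define no T1 contrast for the mixed model. Uneven spacing alone, with four visits, leaves T1 at 4.2-4.9%. Inflation at T1 needs a further assumption, such as post-treatment scores being more alike than pre- and post-treatment scores. Open treatment after T1 could push the error the other way. This objection stands for T1. It does not rescue Tf and T2, where the structure kindest to T1 gives large errors in opposite directions.

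A reader might also infer that each questionnaire is tested twice at three months, leaving a choice of p-value. Taken literally, the change in secondary outcomes "from baseline to follow-up at three months will be analyzed with a linear regression model with treatment as predictor", and six questionnaires (TQ, SSQ12, HADS, VAS, HQ and HUI23) also fall under the mixed model. But the mixed-model sentence can equally be read as assigning the questionnaires to that model and leaving the regression for the rest. Nothing says that the mixed model yields a second three-month p-value, and the list of tests in the Holm family is ordinary analysis-plan content. This part is a request for clarification only.

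Finally, the fixed effects, and perhaps a residual covariance, may be set out in a fuller plan not shown. Their absence is not counted as a fault here. The point concerns the one device that the article does fix.

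**Conclusion.** The point holds as an improvement to the analysis of the secondary questionnaires. The stated random intercept relies on equal correlation that this visit schedule makes doubtful. If visit-specific contrasts are reported from it, the SE ratio at T1 runs from about 0.84 to 1.18 across the four-visit arm-by-visit structures tried (type I error about 10% down to 2%). Under calendar-time decay it is 1.84-2.06 at Tf and 0.77-0.82 at T2. All of these figures rest on assumed correlations, complete data and presumed arm-by-visit terms, and under compound symmetry the error is nil. Neither a definite error at T1 nor duplicate three-month testing is established. The primary TFI regression and the 39 per group do not depend on this model.

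**What to change.** Model the repeated questionnaires with categorical visit, arm-by-visit terms and an unstructured within-patient covariance. State a fallback structure to use if the model does not converge. With T0, Tf and T1 the covariance has 3 × 4/2 = 6 parameters. If T2 is kept it has 4 × 5/2 = 10, and the T2 contrast should be read as post-unblinding and after open treatment. Name the T1 contrast of this model as the single three-month test for each questionnaire, and keep the plain regression for outcomes measured only at T0 and T1. That also settles which three-month result counts.

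The change is to wording, before unblinded data are analysed. It costs a few degrees of freedom and carries some risk of non-convergence with 100 patients. Fitting only the three blinded visits would leave T2 to a separate description, which should be stated.
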